### Recruitment {15}

To ensure adequate recruitment from both the sites, posters containing study details will be displayed, inviting participants to approach the research team. Additionally, the clinicians at both the sites will be sensitized to the study criteria and encouraged to refer potential participants to the research team. In instances where patients have limited time available, the research team will divide the consent and screening process to ensure that patients are not excluded due to time constraints. To ensure fairness, participants who lack access to a laptop or tablet will receive a tablet along with an internet package to facilitate their participation in the study interventions.

## Assignment of interventions: allocation

### Sequence generation {16a}

The participants will be randomly assigned to either V-CCT or active control group in a 1:1 allocation, using a computer-generated randomization table.

### Concealment mechanism {16b}

The randomization table will be stored in password-protected computers, with access restricted to the study coordinator only.

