### Implementation {16c}

Participants will be recruited by the research assistants. Once 16 consecutive participants have been recruited, randomization will be done. The allocation sequence will be created by the statistician. Subsequently, the unblinded study coordinator will notify participants of their assigned allocation group.

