## Assignment of interventions: blinding

### Who will be blinded {17a}

The principal investigator (PI) is blinded to maintain objectivity in overseeing the trial, while the outcome assessors are blinded to ensure unbiased assessment of outcomes. The statistician responsible for randomization is unblinded. Both the co-investigator (Co-I) and project coordinator are unblinded, as they are conducting fidelity checks and in-depth interviews. Research assistants delivering the intervention are also unblinded. Due to the nature of the interventions, participants are not blinded and may be able to identify which intervention they are receiving.

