## Oversight and monitoring

### Composition of the coordinating center and trial steering committee {5d}

The PI and project coordinator at SCARF, the trial’s primary coordinating center, offer the partner site programmatic, financial, and technical support. Additionally, they provide everyday guidance, support and training for the trail’s execution at each site. The trial steering committee, represented by the funder, oversees the study’s progress and provides strategic direction. The research team submits annual reports to the steering committee. The committee will contact the researchers if any clarifications or further information are required. Additionally, there is no formal patient and public involvement in this study.

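### The unblinded coordinator role both holds the allocation table and issues the assignments, and no stated step ties the 16 waiting participants to table lines before the table is seen

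*Protocol article*

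**What the plan says.** Concealment mechanism {16b} is a single sentence. The table is "stored in password-protected computers, with access restricted to the study coordinator only".

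Implementation {16c} gives the sequence of events. Recruitment is in the hands of research assistants. On timing, the section says: "Once 16 consecutive participants have been recruited, randomization will be done". Making the sequence is the statistician's task. As the last step, "the unblinded study coordinator will notify participants of their assigned allocation group".

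Who will be blinded {17a} adds: "The statistician responsible for randomization is unblinded". The same section lists a project coordinator as unblinded, because that role assesses fidelity and carries out interviews. Data management {19} makes the project coordinator responsible for the checking of completed case report forms. The section on the coordinating center {5d} says of the PI and the project coordinator that "they provide everyday guidance, support and training for the trail’s execution at each site".

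Sections 16b and 16c use the title study coordinator. Sections 17a, 19 and 5d use project coordinator. The article does not say whether these are one post or two.

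**The concern.** Concealment has two tasks. It should stop whoever enrols from foreseeing the next assignment, and it should stop whoever applies the sequence from choosing which person receives which assignment. The article's batch procedure deals with the first. For the second it offers only restricted access, and the role with that access is the one that issues the allocations.

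When people are randomized one at a time, the next person takes the next line, and departures are easy to see. Here 16 identified people wait together. Unless their order is fixed first, someone who can see both the list of people and the list of assignments could pair them by judgement, deliberately or not. If that happened, the arms would differ at baseline in ways related to outcome. Neither the intention-to-treat analysis nor assessor blinding would remove that bias, because both act after the groups are formed.

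**Working it through.** The point is procedural, so the main check is to set the statements side by side.

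1. **Who makes the sequence?** The statistician (16c), who is unblinded (17a). A second person therefore knows its content; the restriction in 16b concerns the stored table.
2. **Who can open the stored table?** The study coordinator only (16b).
3. **Who enrols?** Research assistants (16c), who are not said to have table access.
4. **When is randomization done?** After 16 consecutive participants have been recruited (16c). Membership of the batch is then settled.
5. **Who passes on the result?** The study coordinator, unblinded (16c).
6. **What links a person to a line?** Nothing is stated. The word consecutive describes how the 16 are recruited; no sentence says that consent order is the order of the table.
7. **What might the coordinator know about the 16?** If the study and project coordinator are the same person, that person supports the sites daily (5d) and oversees the checking of case report forms (19). The article does not say that this checking precedes allocation.

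Items 3 and 4 protect the decision to enrol. Items 2, 5 and 6 together leave the pairing of people with lines unprotected on the stated text.

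The timing of the sequence can be read in two ways:

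- *One table made in advance.* The coordinator can see coming assignments while a batch fills, and sees both lists when it is complete.
- *A sequence made for each batch after recruitment.* Coming assignments are not visible. The pairing is protected only if the statistician also attaches IDs to lines before the coordinator has access, and this is not stated.

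**Size, as a worst-case illustration only.** The inputs from the article are 160 participants, batches of 16 and a planned effect of 0.64 (Sample size {14}, Implementation {16c}). Three further inputs are assumptions: 8:8 batches, one swapped pair per batch always favouring the same arm, and a gap of 1 SD in expected outcome between the two people swapped.

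- Batches: 160 / 16 = 10.
- Shift in each arm mean within a batch: 1 / 8 = 0.125 SD, in opposite directions.
- Shift in the between-arm difference: 2 × 0.125 = 0.25 SD.
- Relative to the planned effect: 0.25 / 0.64 = 0.39.

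In general, with k affected batches out of 10 and a gap of g SD, the shift over 80 per arm is 2 × k × g / 80 = k × g / 40. This gives 0.25 for k = 10 and g = 1; 0.125 for k = 10 and g = 0.5; and 0.025 for k = 1 and g = 1. Swaps with no consistent direction average to zero.

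**The case against.** The strongest reply is that concealment mainly protects enrolment, and on the text enrolment is protected. Recruiters are not said to have table access and the whole batch is in place before randomization. This stands. A reader might infer that allocation concealment fails in this trial; the documents do not support that.

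Second, 16c gives the coordinator one task, notification, and speaks of a group already assigned. Nowhere is the coordinator said to recruit, screen, judge eligibility or match people to lines. This also stands. What can be said is that no stated step prevents the coordinator from doing the matching, not that the coordinator does it.

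Third, it is tempting to picture a complete 160-line table held from the start by someone who runs both sites. The article leaves open whether the sequence is made once or per batch, and that the two coordinator titles denote one person is a likely inference, not a stated fact.

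Fourth, one might suppose a motive, such as placing better attenders in V-CCT because dropout is feared there. The 50% dropout in Sample size {14} is assumed for the whole sample, and the retention section {18b} expects the schedule to cause dropout in either arm. The text gives no such motive.

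Fifth, a condensed article may leave the linking of IDs to lines to the full protocol or a procedure document. Absence of that detail alone would be no finding. But the article does answer 16b and 16c, and the arrangement it states puts custody of the table and issue of the allocations in one role. That objection to the stated method survives.

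**Conclusion.** The point holds in limited form. As written, one unblinded role has access to the stored table and issues the allocations, and no stated step locks the order of the 16 before the table can be seen. This is a correctable weakness in the mechanism, worth changing because the change is nearly free. It is not evidence of subversion or of failure at enrolment.

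The size is unknown. The figure of 0.25 SD is an upper illustration that depends on a same-direction swap in every batch, a 1 SD gap and 8:8 batches; the article states no blocking. It should not be read as an expected bias, nor taken to mean that all 160 assignments are compromised.

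The conclusion rests on 16b and 16c describing the actual procedure. If the statistician already attaches IDs to a sequence made for each batch before the coordinator has access, the weakness reduces to unclear wording. If the two coordinator titles are different people, the argument from daily site contact falls away, but custody and issue of the allocations still sit together.

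**What to change.** Amend Concealment mechanism {16b} and Implementation {16c} as follows:

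- The statistician, who is already unblinded, holds the sequence. Alternatively it is loaded into a randomization module in REDCap, which the trial already uses, with the table hidden from site staff and the coordinator.
- Once all 16 in a batch have consented and completed baseline, the coordinator submits a locked, dated list of the 16 IDs in consent order.
- The statistician or the system returns the assignments for that batch only, and both lists are filed. The coordinator then notifies participants, as now planned.
- State whether the sequence is made once or per batch.
- Reconcile the titles study coordinator and project coordinator across 16b, 16c, 17a, 19 and 5d.

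The cost is about ten exchanges (160 / 16) or a one-off REDCap set-up, with a short delay per batch. The sample size does not change. The procedure can be applied to any batch not yet randomized.

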### Implementation {16c}

Participants will be recruited by the research assistants. Once 16 consecutive participants have been recruited, randomization will be done. The allocation sequence will be created by the statistician. Subsequently, the unblinded study coordinator will notify participants of their assigned allocation group.

## Assignment of interventions: blinding

### Who will be blinded {17a}

The principal investigator (PI) is blinded to maintain objectivity in overseeing the trial, while the outcome assessors are blinded to ensure unbiased assessment of outcomes. The statistician responsible for randomization is unblinded. Both the co-investigator (Co-I) and project coordinator are unblinded, as they are conducting fidelity checks and in-depth interviews. Research assistants delivering the intervention are also unblinded. Due to the nature of the interventions, participants are not blinded and may be able to identify which intervention they are receiving.

### Procedure for unblinding if needed {17b}

If harm occurs to a participant, unblinding is permissible and will be managed in accordance with specific safeguarding policies and standard operating procedures (SOPs) established.

## Data collection and management

### Plans for assessment and collection of outcomes {18a}

All assessment tools have been translated into the local language. The study team has undergone training in good clinical practice and outcome assessment. Practice sessions for outcome assessments were conducted and overseen by SG, ensuring good inter-rater reliability. Facilitators of the intervention and active control sessions received training from [name], Metro South Health Service, Brisbane, and SG. Information will be gathered through paper case report forms (CRF) and subsequently entered into an electronic database known as REDCap. The researchers are responsible for creating and managing the REDCap database, and data cleansing will occur once the study concludes. Those interested can request access to the data collection forms from the authors.

The data assessment tools used in the study include:

*Brief Assessment of Cognition in Schizophrenia (BACS)*: BACS includes tests of verbal memory (Verbal Memory Task), verbal working memory (Digit Sequencing Task), motor/speed (Token Motor Task), verbal fluency (Verbal Fluency Task), attention/information processing (Symbol Coding Task), and executive function (Tower of London Task). BACS scores will be converted to z-scores to provide a standard metric for combining test scores into domains and comparing performance over time, relative to healthy persons [17].*Socio-Occupational Functioning Scale (SOFS)*: SOFS is a brief and comprehensive scale that has been validated in India. It consists of 14 items to measure the social functioning of patients with schizophrenia across three domains, namely adaptive living skills, social appropriateness, and interpersonal skills. The items are scored on a 5-point scale, where “1” indicates no impairment, and “5” indicates extreme impairment. The ratings may be provided by mental health professionals, family members, or other care providers familiar with the patient. SOFS demonstrates good internal consistency (*α* = 0.91) and test–retest reliability, with intraclass coefficient of 0.95. It is reported to have satisfactory content validity, with several other types of validities established, including concurrent validity, criterion validity, discriminant validity, and construct validity [19].*Socio-demographics Questionnaire*: a questionnaire to collect socio-demographic information from all participants at baseline.*Subjective Scale to Investigate Cognition in Schizophrenia (SSTICS Tamil version)*: SSTICS is a self-report measure that is brief, with 21 items to assess complaints about memory, attention, praxia, and executive function in persons with schizophrenia. It demonstrates good internal consistency (*α* = 0.86) and test–retest reliability (rs = 0.82). The scale takes approximately 6 min to complete [18].

Secondary outcome measures include:

*Manchester Short Assessment of Quality of Life (MANSA)*: The MANSA is a brief instrument for assessing quality of life focusing on satisfaction with life as a whole and with life domains. It has 16 items and is rated on a 7-point Likert scale. Cronbach’s alpha for satisfaction ratings was 0.74. Tamil version of MANSA is available and has been used for assessing subjective quality of life in persons with psychosis in the local setting [20].*Rosenberg Self-Esteem Scale (RSES)*: This is a self-report measure that consists of 10 items that assess the self-esteem of the respondent. The items are scored on a 4-point scale, ranging from strongly agree to strongly disagree. The test–retest reliabilities range from 0.82 to 0.88 and Cronbach’s alpha range from 0.77 to 0.88. Validity was established by its correlation with the Coopersmith Self-Esteem Inventory. Several studies have established the psychometric properties of the RSES [21].

### Plans to promote participant retention and complete follow-up {18b}

Both intervention and active control sessions will be delivered virtually for 6 weeks, consisting of two sessions per week. This schedule may potentially result in participant dropout due to various reasons. To ensure better retention rates and complete follow-up, the facilitators of both the intervention and active control groups will create an independent WhatsApp group for participants in each arm where all updates regarding the sessions will be posted.

Participants who drop out will still be invited to the end-line and follow-up assessments, unless they explicitly express disinterest. Flexible scheduling options will be provided for assessments and intervention sessions to accommodate participants’ availability based on the consensus of the group.

A subsample of participants who have dropped out of the intervention will be approached for a semi-structured interview to understand their experiences, barriers, and facilitators in attending the sessions virtually.

### Data management {19}

The paper-based case report forms (CRFs) used for data collection will be securely stored in locked cabinets at both sites. The project coordinator will oversee the verification of completed CRFs. Should any errors be identified, the CRFs will be returned to the respective assessor for necessary corrections. Following final verification, the data will be inputted into the REDCap electronic database. Co-investigators (Co-I) will then cross-reference the entered data with the source CRFs to ensure accuracy. Detailed data management protocols are outlined in the “Document Completion, Transport, and Storage SOP” and “Data Entry SOP” established by each site, which can be provided upon request from the authors.

A session log will be maintained by the facilitators of both the intervention and control arm. It will record information on participant involvement, compliance with homework (HWs), duration of the session, any challenges observed during the session, and how they were handled. Also, participant attendance will be recorded in each session, and the reasons for absence during a particular session will be documented when they attend next session, or the facilitator will contact the participant over the phone and document the reason for absence. The reasons for the same will be documented in the session log.

### Assessing fidelity of the sessions

All sessions will be recorded after obtaining consent from the participants. The Co-Is and project coordinator would randomly choose 3 out of 12 recordings and assess the fidelity using the fidelity checklist.

### Confidentiality {27}

To safeguard patient confidentiality, all patient-related information will undergo pseudonymization, with each participant assigned a unique ID number. Access to the password-protected folder containing patient personal data (such as participant name and contact information) and the corresponding ID list will be restricted to the study team. Hard copies of data, including case report forms, consent forms, patient receipts, and sociodemographic forms, will be stored in locked file cabinets at both sites. Evaluations will occur in separate rooms from both participants and researchers to enhance confidentiality. Control and intervention sessions will be conducted via a secure Zoom platform to ensure data security, with group facilitators sharing Zoom links with group members via WhatsApp. Participants will be instructed not to share the link with anyone outside the group. Transcripts will be examined on secure computers accessible only to research team members. Any participant remarks quoted in the final report will remain anonymous.

### Plans for collection, laboratory evaluation, and storage of biological specimens for genetic or molecular analysis in this trial/future use {33}

This is not applicable; this study does not collect any biological data.

## Statistical methods

### Statistical methods for primary and secondary outcomes {20a}

Statistical Package for Social Sciences (SPSS) Version 21.0 will be used to analyze the data. Descriptive statistics will be used to present sociodemographic information, continuous variables will be characterized using measures of central tendency and variability, and nominal and ordinal data will be presented as proportions (frequency). The statistical tests for inferential analysis will be chosen based on discovered distributions (parametric or non-parametric), which will be assessed using probability functions and normality tests on histograms. The effectiveness of V-CCT will be evaluated using an intention-to-treat (ITT) analysis. The mean, standard deviations, and interquartile range for each of the three time points—baseline, 6 weeks, and 12 weeks—will be computed. The significance of the variations in the means (or other parameters) of the measured outcomes will be tested by the analysis.

The primary outcomes will be the BACS scores on various domains of cognition and functioning as assessed using SOFS. Self-esteem and quality of life are the secondary outcome measures. The effect size and 95% CI will be calculated to establish the superiority of the intervention arm over the control arm. Additionally, qualitative data obtained from the semi structured interview will be coded and analyzed.

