### Outcomes{12}

Quantitative outcome measures will be assessed at three distinct time points: baseline (v0), post-intervention (v6) at 6 weeks, and at follow-up, which occurs 3 months from baseline (v12).

The primary outcome measures will include assessments of cognition using Brief Assessment of Cognition in Schizophrenia (BACS) [17] and Subjective Scale to Investigate Cognition in Schizophrenia (SSTICS Tamil version) [18] and functioning using Socio-Occupational Functioning Scale (SOFS) [19], at 6 weeks.

Secondary outcome measures will include assessments of quality of life using the Manchester Short Assessment of Quality of Life (MANSA) [20] and self-esteem using Rosenberg Self-Esteem Scale (RSES) [21].

All the measures will be repeated at 12 weeks to assess if the treatment effects are sustained.

The sociodemographic details of the participants will be collected at baseline and summarized as means and proportions. The primary and secondary outcome measures will be presented using mean and standard deviation, and comparisons will be made between the treatment and control arm at 6 weeks and 12 weeks. A subgroup of 20 participants, randomly selected from the intervention group, will be asked to participate in qualitative interviews at the conclusion of the 6-week intervention. These interviews aim to explore participants’ experiences with the intervention, including identifying facilitators and barriers, suggesting adaptations, and assessing the practical delivery of the intervention.

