### Sample size {14}

A Sample size of 104 participants (52 in each arm) is required based on the outcome indicators of cognitive performance with an effect size of 0.64 between the intervention and control groups, with 90% power and 5% alpha error using R 4.0.3 “pwr.t.test” software. A dropout rate of 50% has been assumed based on previous experiences and studies done using CCT. Therefore, the total number of recruited subjects at both sites will be 156 rounded up to 160 participants in total [22].

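### The protocol gives two different lists of primary outcomes and no rule for which must succeed, while the sample size allows for only one two-sided 5% test

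*Protocol article*

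**What the plan says.** **Objectives {7}.** Cognition and socio-occupational functioning are joined in one primary objective.

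**Outcomes {12}.** The primary measures are BACS together with the "Subjective Scale to Investigate Cognition in Schizophrenia (SSTICS Tamil version) [18] and functioning using Socio-Occupational Functioning Scale (SOFS) [19], at 6 weeks". The 12-week repeat is there to see whether effects last.

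**Plans for assessment and collection of outcomes {18a}.** Six BACS tests are listed, each tied to a cognitive function. Their z-scores are to be combined into domains. No composite is named as primary. SSTICS is described before the line that introduces the secondary measures.

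**Statistical methods {20a}.** "The primary outcomes will be the BACS scores on various domains of cognition and functioning as assessed using SOFS". Listed there as secondary are quality of life and self-esteem. SSTICS does not appear. On the claim itself: "The effect size and 95% CI will be calculated to establish the superiority of the intervention arm over the control arm".

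**Sample size {14}.** The stated requirement is 52 per arm, 104 in all, for cognitive performance. The inputs are given as "with an effect size of 0.64 between the intervention and control groups, with 90% power and 5% alpha error".

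**The concern.** Two things are at stake.

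First, the protocol fixes the primary set twice, and differently. SSTICS is primary in one section and has no status in the other. BACS is an instrument in one and a set of domain scores in the other. Where SSTICS or a single BACS domain departs from the remaining results, the primary conclusion could depend on which section is followed.

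Second, both lists are plural, yet the design has one effect size, one alpha and one power figure. With several primaries, these error rates mean something only once it is known which outcomes must succeed for V-CCT to be called superior. The text does not say, so it does not exclude a claim resting on one favourable domain.

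**Working it through.** **1. Reproduce the plan's own figure.** Inputs from Sample size {14}: d = 0.64, alpha 5%, power 90%. Sidedness is not stated; two-sided is assumed.

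n per arm = 2(z₀.₉₇₅ + z₀.₉₀)² / d² = 2(1.960 + 1.282)² / 0.64² = 21.02 / 0.4096 = 51.3, so 52 per arm and 104 in total, as stated.

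The noncentral t calculation gives 53 per arm, and 89.8% power at 52. One-sided 5% would need only 42 per arm and does not match. The stated size therefore belongs to one two-sided test at the full 5%.

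**2. Count the primary tests (k).** The protocol gives no number.
- BACS as one score plus SOFS: k = 2. With SSTICS: k = 3.
- Each of the six BACS tests plus SOFS: k = 7. With SSTICS: k = 8.
- If tests are merged into fewer domains, k lies between these.

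**3. If success on any one is enough.** Under independence and no effect, the chance of at least one two-sided p < 0.05 is 1 − 0.95^k. Counting only results in V-CCT's favour it is 1 − 0.975^k, against 2.5% for one test.

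| k | Two-sided, independent | Favouring V-CCT, independent |
|---|---|---|
| 2 | 9.8% | 4.9% |
| 3 | 14.3% | 7.3% |
| 7 | 30.2% | 16.2% |
| 8 | 33.7% | 18.3% |

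The outcomes are likely to be correlated, but the documents give no correlation. Simulation of equally correlated normal statistics (400,000 draws) for k = 7, with assumed values:

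| Correlation | Two-sided | Favouring V-CCT |
|---|---|---|
| 0.3 | 27.1% | 13.7% |
| 0.5 | 22.9% | 11.5% |
| 0.7 | 17.8% | 8.9% |
| 0.9 | 11.6% | 5.8% |

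Even k = 2 at correlation 0.9 gives 7.0% two-sided and 3.5% in V-CCT's favour.

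**4. If all must succeed.** Alpha stays at or below 5%. If each outcome has 90% power and they are independent, overall power is 0.9^k: 81% (k = 2), 73% (k = 3), 48% (k = 7), 43% (k = 8). Positive correlation raises these, but they reach 90% only if the outcomes move together completely.

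**5. If Bonferroni is used.** Power of each test at d = 0.64 and 52 per arm (noncentral t), and the number per arm for 90%:

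| k | Alpha per test | Power at 52 per arm | Per arm for 90% |
|---|---|---|---|
| 2 | 0.025 | 83.7% | 62 |
| 3 | 0.0167 | 79.5% | 68 |
| 7 | 0.0071 | 69.7% | 79 |
| 8 | 0.00625 | 68.1% | 81 |

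**The case against.** The best defence is that a multiplicity method is commonly left to an SAP, which is not shown, and that this is a condensed article. That stands: the absence of a named adjustment is not in itself a fault here. It does not cover the primary list, which the article states twice in conflicting forms, or a sample size that fits only one test at full alpha.

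Four stronger readings are tempting, and the documents do not support them.

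- **That there are seven or eight primary tests.** The statistical section gives no number of domains, and combining z-scores into domains could yield fewer than six.
- **That the plan lets one significant domain establish superiority.** No such rule is written. The joint primary objective equally allows a reading in which cognition and functioning must both succeed, and then the loss is in power rather than alpha.
- **That the false-positive rate is 30% to 34%.** Those figures assume independence, the highest counts and errors in either direction. For a claim that V-CCT is superior, the one-directional figures are the relevant ones, and they are about half as large.
- **That a BACS composite is what was powered.** The sample size section speaks of cognitive performance indicators in the plural and names neither instrument nor composite.

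It is also fair to say that the 6-week time point is already set in the outcomes section. The two lists need not lead to different conclusions; they do so only if the outcomes on which they differ give different results.

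**Conclusion.** The concern holds in this form: the two sections disagree on the primary outcomes, both name several, and no success rule is stated, while the trial is sized for one two-sided 5% test with 90% power. None of the three rules checked keeps both figures. An any-success rule raises the false-positive rate in V-CCT's favour to about 5% to 18% under independence (9% to 14% for 7 tests at correlations of 0.7 to 0.3), against 2.5%. An all-must-succeed rule or Bonferroni keeps alpha but loses power.

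This rests on an inferred count of 2 to 8, assumed correlations, two-sided testing, and an effect of 0.64 on every outcome in the power figures. The count changes the size of the problem, not its existence, since two tests are enough to produce it. All power figures take the planned 52 per arm as evaluable. The point should be settled before outcome data are seen.

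**What to change.** Use one identical primary list in Objectives {7}, Outcomes {12}, the assessment tools section {18a} and Statistical methods {20a}. One workable form, among several:

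1. Name a single primary cognitive score at 6 weeks, tested at two-sided 5%. A BACS composite z-score is one candidate; the sponsor would need to confirm that the 0.64 applies to it.
2. Test SOFS at 6 weeks at the full two-sided 5%, only if step 1 succeeds. This keeps both parts of the primary objective without splitting alpha.
3. Make the individual BACS domains and SSTICS secondary, reported with estimates and intervals but no superiority claim.

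This needs no extra participants. It costs revised wording, a registry update, and the ethics committee and funder approval that the section on protocol amendments {25} requires for changes after the start. The price is that one favourable domain, or SOFS alone, can no longer carry the claim.
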